## Patient selection and enrollment

### Patient number

Eligible patients will be randomized in two arms in a ratio of 2:1 to reach an approximate total of 546 patients. The sample size ratio is 2:1 (study arm is 2, control is 1), treatment duration is 1 year. Based on data of the 3-year DFS rate from our previous retrospective study, the proportion of control arm is 0.55 (55%) and of the study arm is 0.7 (70%) with a significance level of 0.05 and a power of 80%.

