**Fig. 2 Fig2:**
[figure not shown]
Flowsheet for pre/post-treatment investigations

Patient eligibility criteria will be established before treatment enrollment.

Following the completion of an adjuvant oxaliplatin-based regimen within 3 weeks with no evident disease recurrence, all eligible patients will be randomly assigned to either arm A (maintenance therapy) or arm B (observation arm) in a 2:1 ratio (364 and 182 patients in the tegafur-uracil and observation groups, respectively). Treatment in arm A will be started within 7 days of the randomization.

If the patients report disease recurrence, intolerable toxicity, or consent withdrawal or are removed according to the investigator’s discretion during the study period, they will be withdrawn from the study. If a patient wishes to discontinue the study, the corresponding data will not be reused, and the patient will not be allowed to re-enter the study.

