Screening procedures will be performed before the first treatment according to the assessment schedule within the required timeline.Demographic and past medical historyA complete medical history will be obtained at the screening visit. The medical history will include demographic information as well as any information pertinent to a CRC diagnosisPhysical examination, vital signs, and performance statusPhysical examination will be conducted, and vital signs and the performance status will be reported within 14 days before the first treatment and be repeated at every visit until study completion.The vital signs, including height, weight, blood pressure, and performance status, will be recorded according to the ECOG ScaleHematological and biochemical testsHematological and biochemical tests will be performed within 14 days before the first treatment. If any required hematological or biochemical values do not meet the eligibility criteria, the tests will be repeated before enrollment. If the tests performed within 7 days before the first treatment fulfill the eligibility criteria, tests are not required on day 1 of treatment.The hematological test comprises complete blood count (CBC) and differentiation count (D/C). CBC includes hemoglobin, hematocrit, erythrocytes, leukocytes, neutrophils, and platelets; The D/C will be calculated to obtain the ANC.The biochemical test measures albumin, alkaline phosphatase, ALT, AST, bilirubin (total and direct), blood urea nitrogen (BUN), and creatinineCarcinoembryonic antigenCarcinoembryonic antigen (CEA) will be assessed every 3 months before the first treatment and will be repeated every 3 months in the first and second years and every 6 months thereafterComputed tomography or magnetic resonance imagingComputed tomography (CT) or magnetic resonance imaging (MRI) will be annually performed in the first 2 years or if disease recurrence is suspected. The acceptable window for scheduling the imaging studies is ±1 week. Subsequently, CT or MRI will be performed only on suspected disease recurrence thereafterAbdominal echoAbdominal echo will be performed every 6 months. However, its actual implementation will be based on clinical practice. The schedule of CT or MRI and abdominal echo are crossed over, and the typical interval is 6 months. CT or MRI is the main examination when the schedule is duplicatedChest X-rayChest X-ray will be annually performedAdverse eventsAEs will be recorded from the first treatment to treatment completion

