
### Efficacy measurements and endpoints

In this study, we set 3-year DFS and 5-year OS as the primary endpoints and the differences the difference in survival distributions between two groups were analyzed using the log-rank test.Three-year disease-free survival (DFS)CEA and CT or MRI scan will be performed within 28 days before the treatment. The CEA level will be the efficacy measurement for endpoints and will be performed within every 3 months before the first treatment and repeated every 3 months in the first and second year and every 6 months thereafter. CT or MRI can be performed annually in the first 2 years or on suspected disease recurrence. The acceptable window for scheduling the imaging studies is ±1 week. Thereafter, CT or MRI will be performed only on suspected disease recurrence. DFS will be measured from start from the date of randomization to the date of disease recurrenceFive-year overall survival (OS)OS will be measured from the start from the date of randomization to the date of deathSafety profileHematological and biochemical tests should be closely monitored during the treatment period because bone marrow depression, liver dysfunction, dehydration, anorexia, nausea, vomiting, and other AEs that have been reported in clinical treatment. The evaluation results would be included in the date or symptoms mentioned in the package insert

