Statistical analysesDemographic and baseline measuresAll demographic and baseline data will be summarized and listed in detail. For continuous variables, the descriptive statistics, including the patient number, mean, median, standard deviation, and range (minimum-maximum) will be presented; frequency tables will be displayed for categorical data. If demographic and baseline measures are significant, their inclusion in the analysis model will be consideredThree-year disease-free survival (DFS)Three-year DFS will be defined as the percentage of patients alive without disease recurrence at 3 years measured from the randomization date. The 3-year DFS will be evaluated using the Kaplan-Meier method, and the analysis will be presented in descriptive statistics, presented by a point estimate and 95% confidence interval. The results will be summarized in the form of the sample size, mean, standard error, median, percentiles, and range by descriptive statistical methodsFive-year overall survival (OS)Five-year OS will be defined as the percentage of patients alive at 5 years measured from the randomization date. The 5-year OS will be evaluated using the Kaplan-Meier method, and the analysis will be presented in descriptive statistics, presented by a point estimate and 95% confidence interval. The results will be summarized in the form of the sample size, mean, standard error, median, percentiles, and range by using descriptive statistical methodsSafety profileAEs will be summarized using NCI-CTCAE v4.03 and the preferred term. The incidence and percentage of patients with at least one occurrence of a preferred term will be included according to the most severe NCI-CTCAE v4.03 grade. Laboratorial toxicity will be presented according to the highest NCI-CTCAE v4.03 grade by cycle

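### Covariate adjustment hinges on whether baseline measures turn out significant, which leaves the choice between adjusted and unadjusted DFS comparisons open after data are visible

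*Protocol article*

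**What the plan says.** Under *Statistical methods and sample size determination*, in the paragraph on demographic and baseline measures, the article states "If demographic and baseline measures are significant, their inclusion in the analysis model will be" considered. It does not say what the measures must be significant for, at what level, which measures are meant, or which model they would enter.

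The between-arm test is named elsewhere. *Efficacy measurements and endpoints* says "the difference in survival distributions between two groups were analyzed using the log-rank test", with no strata or covariates mentioned. The DFS paragraph of the statistics section gives only Kaplan-Meier estimates with a 95% confidence interval and descriptive summaries.

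Three further statements bear on the point:

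- *Study design* calls the trial open-label.
- The statistics section promises a comprehensive analysis plan before database lock.
- *Inclusion criteria* admit stage III disease across T1-4 and N1-2, so T and N category must be known at entry. Of the screening history the article says "The medical history will include demographic information as well as any information pertinent to a CRC" diagnosis.

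**The concern.** This is a stated selection principle, not an omitted detail, and it is a poor one on either reading of *significant*.

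- **Imbalance between arms.** Under randomization any imbalance is chance, and its p-value says nothing about whether the factor predicts recurrence. A strong predictor that happens to be balanced is left out, although adjusting for it would still add power. An irrelevant factor that happens to be imbalanced is let in.
- **Association with outcome.** The covariates are then chosen from the outcome data themselves.

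On both readings the trigger is read from trial data, and *considered* leaves the last step to judgement. A log-rank test has no model for a covariate to enter, so the two sections together do not identify one primary comparison. An analysis plan due only before database lock need not precede sight of outcomes by arm when treatment is open. At stake are the type I error of a confirmatory phase III comparison and some power.

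**Working it through.** **Inputs from the article.** Allocation and size: "Eligible patients will be randomized in two arms in a ratio of 2:1 to reach an approximate total of 546 patients". Three-year DFS: "the proportion of control arm is 0.55 (55%) and of the study arm is 0.7 (70"%). Alpha is 0.05 (sidedness not stated; two-sided assumed here) and power 80%.

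**Inputs assumed.** The article gives no prognostic strengths, so every figure that depends on them is conditional.

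**The plan's own figure.** With two proportions, 2:1, two-sided, the pooled proportion is (0.55 + 2 × 0.70)/3 = 0.65. The control arm needs

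[1.96 × √(0.65 × 0.35 × 1.5) + 0.842 × √(0.55 × 0.45 + 0.70 × 0.30/2)]² / 0.15² ≈ 120.2, so 121, and 363 in total.

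The stated 546 is not reproduced. That is a separate matter, but it sets the power available here:

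- Design hazard ratio: ln 0.70 / ln 0.55 = 0.597.
- Events by 3 years: 546 × (2/3 × 0.30 + 1/3 × 0.45) = 191.1.
- Power: Φ(√(191.1 × 2/9) × |ln 0.597| − 1.96) ≈ 92%.

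**How often an imbalance trigger fires.** With four independent factors each tested at 5%, 1 − 0.95⁴ = 18.5% of trials show at least one significant imbalance by chance.

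**Simulation settings.**

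- *Setting A:* 364 v 182 patients, exponential times censored at 3 years, control DFS 55%. N2 in 40% (hazard ratio 2.0, or 2.5 in the stronger case), T4 in 25% (1.7, or 2.0), and two weaker factors.
- *Setting B:* same size and ratio, 3 to 5 years of follow-up, log-rank tests. Power uses one binary factor of 35% prevalence. The free-choice runs use two factors (hazard ratios 2.0, 1.5) or four (2.0, 1.5, 1.5, 1.3).

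**Two-sided type I error, nominal 5%.**

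| Strategy | Result |
|---|---|
| Fixed unadjusted or fixed adjusted test | 4.7 to 5.2% |
| Mechanical: adjust only if arms differ at p<0.05 | 4.1 to 5.5% across runs |
| Most favourable of 7 models (A) | 7.4%; stronger factors 8.5% |
| Most favourable of 4 models (A, repeat run) | 7.8 to 8.2% |
| Most favourable of unadjusted and all stratified versions (B) | 7.3% with two factors; 10.0% with four |

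In the direction of benefit alone, the last row is 3.8% and 5.1% against 2.5%.

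**Power.**

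| True hazard ratio | Assumed factors | Unadjusted | Prespecified adjustment | Gain (points) |
|---|---|---|---|---|
| 0.597 (design) | A | 92.6% | 94.0% | 1.4 |
| 0.597 (design) | A, stronger | 90.3% | 93.6% | 3.3 |
| 0.655 | A | 80.0% | 83.4% | 3.4 |
| 0.655 | A, stronger | 77.1% | 82.7% | 5.6 |
| 0.70 | B, factor 1.5 | 78.3% | 79.5% | 1.2 |
| 0.70 | B, factor 2.0 | 76.3% | 79.5% | 3.2 |
| 0.70 | B, factor 3.0 | 70.4% | 78.6% | 8.2 |

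In setting B at 0.597 the gain is 0.3, 0.8 and 2.7 points for the three factor strengths. A repeat of setting A at 0.655 gave gains of 2 to 5 points. The mechanical rule recovers almost none of this: at 0.655 it reaches 80.3% (80.0% unadjusted) and 77.9% (77.1% unadjusted).

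**The case against.** The strongest reply is that the sentence may govern only a supportive model, since neither Kaplan-Meier estimation nor the log-rank test takes covariates, and that the promised analysis plan can fix the details. The first part is possible, but the article does not say it. It refers to the analysis model without naming one. The second part is fair for a list of covariates. It does not excuse a stated principle, which a plan written to follow the article would carry forward.

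It is also fair that an unstratified log-rank test is valid under randomization, that the error figures describe a choice nobody has announced, and that power at the design effect is ample either way. These points limit the size of the problem without removing it.

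A reader might draw four stronger conclusions, which the documents do not support:

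- *Randomization ignores stage.* The article gives only the 2:1 ratio. Silence in a condensed article does not show that there are no strata.
- *The rule as written inflates type I error.* Applied mechanically to imbalance, it does not. The inflation needs discretion used in one direction.
- *The unadjusted test over-rejects when N category is imbalanced.* This is true within the few trials with that imbalance. But it describes the unadjusted test in exactly the trials where the rule would prompt adjustment, so it does not count against the rule.
- *The unadjusted hazard ratio is biased toward 1.* The difference from the adjusted one reflects non-collapsibility. The two are different estimands, and neither is an error.

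**Conclusion.** The concern holds in limited form. The article ties adjustment to observed significance plus discretion, and so does not fix whether the primary DFS comparison is adjusted.

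The two-sided type I error of about 7 to 8.5%, or 10% with four factors, is an upper range for what the wording permits, not a forecast. It rests on assumed prognostic strengths and on always taking the most favourable model. The power argument is secondary: about 1.5 to 3 points at the design hazard ratio of 0.597 under the N and T assumptions, where power is already at or above 90%. The larger gains belong to effects smaller than the one the trial was designed for. The availability of T and N category is inferred from the eligibility criteria, because the article does not list them as recorded baseline items.

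**What to change.** Delete the sentence that makes adjustment depend on significance. Before any outcome data by arm are reviewed, state that:

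- the primary DFS comparison is a log-rank test stratified by N category (N1 v N2) and T category (T4 v T1-3), plus any factor used to stratify randomization;
- the hazard ratio and 95% confidence interval come from a Cox model on the same factors;
- these factors are used whatever the baseline table shows;
- the unstratified log-rank test and the unadjusted hazard ratio are reported alongside.

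If the sponsor prefers an unadjusted primary test, saying so firmly would also close the choice, at the price of the power gain.

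The cost is one or two sentences and a slightly larger model. T and N category are already needed for eligibility; the case report form should be checked to confirm that it records them. The small downside is that the adjusted hazard ratio is conditional on stage, which is why the unadjusted one belongs beside it.

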## Objective

### Primary objective

To compare the 3-year DFS of tegafur-uracil following an adjuvant oxaliplatin-based regimen with that of an adjuvant oxaliplatin-based regimen in patients with stage III colon cancer after radical resection.

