#### Statistical methods and sample size determination

This is an open-label, randomized, comparative, double-arm, multicenter, phase III study of tegafur-uracil following an adjuvant oxaliplatin-based regimen in patients with stage III colon cancer after radical resection.Statistical evaluationStatistical analysis methodsA comprehensive statistical analysis plan will be prepared before database lock. The patients will be categorized into the Full Analysis Set (FAS), per protocol (PP), and safety populations according to the following definitions:Full Analysis Set (FAS):The FAS is defined as containing all registered and randomized patients who received at least one dose of the study treatment without major protocol violations, such as noncompliance with the eligibility criteria, or other major violations (defined before database lock) during the studyIntent-to-treat (ITT):The ITT population is the subset of the FAS population, and as all randomized patients irrespective of treatment receivedPer protocol (PP):The PP population is the subset of the ITT population and subjects who complete 12 months of tegafur-uracil treatment/observation with at least one biomarker assessment post treatment. The subject with confirmed early disease recurrence/relapse would be included in the PP population. The patients with confirmed early disease recurrence and relapse will be included in the PP population.All the efficacy endpoints will be analyzed in the FAS and PP populations. The main assessment will be performed on the basis of the PP population.The safety population is defined as all patients who are exposed to at least one dose of the study treatment and who are available for obtaining follow-up safety information

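### Disease-free survival has two incompatible event definitions: one section counts death without recurrence as a failure, while the section that names the log-rank test ends DFS at recurrence only

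*Protocol article*

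**What the plan says.** All references are to the protocol article.

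- **Primary objective:** "To compare the 3-year DFS of tegafur-uracil following an adjuvant oxaliplatin-based regimen" with that of the oxaliplatin-based regimen alone.
- **Statistical methods and sample size determination (DFS item):** "Three-year DFS will be defined as the percentage of patients alive without disease recurrence at 3 years measured from the randomization date". The same item continues: "The 3-year DFS will be evaluated using the Kaplan-Meier method". It asks for a point estimate and 95% confidence interval and names no test.
- **Efficacy measurements and endpoints:** this section names 3-year DFS and 5-year OS as primary endpoints and says that "the difference in survival distributions between two groups were analyzed using the log-rank test". It then measures DFS from randomization to the date of recurrence. Death is not mentioned for DFS, although the next item ends OS at death.
- **Analysis populations:** "The main assessment will be performed on the basis of the PP population". Membership of that population requires completing 12 months of treatment or observation, with one exception: "The patients with confirmed early disease recurrence and relapse will be included in the PP population". Early death is not excepted.
- **Patient number:** 3-year DFS of 55% (control) and 70% (study). The section does not say which event definition these rates use.

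**The concern.** The two DFS rules classify the same patient differently. Someone who dies without recurrence at month 20 has failed under the statistical section. Under the efficacy-endpoint section that patient has no event. In a log-rank test built on the latter rule, the usual consequence is censoring at death, which makes the endpoint time to recurrence and not disease-free survival.

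If each section is followed as worded, the reported estimate and the p-value for the primary endpoint count different events. This matters here because patients may be up to 80 years old, so some deaths without recurrence are to be expected, and because one arm takes a cytotoxic drug for a year while the other is observed, so such deaths need not be balanced. The trial is open-label and the analysis plan is promised only before database lock. The choice between the two definitions could therefore be made when outcomes are already visible.

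**Working it through.** **1. The definitions side by side**

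| Patient's course | Statistical section | Efficacy-endpoint section |
|---|---|---|
| Recurrence | failure | event |
| Death without recurrence | failure | not an event |
| Alive, no recurrence | not a failure | not an event |
| Analysis named with it | Kaplan-Meier, 95% CI | log-rank test |

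They differ only in the second row, and no other section settles it.

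**2. The plan's own figures**

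With constant hazards, h = −ln(S)/3:

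- control: −ln(0.55)/3 = 0.199 per year
- study: −ln(0.70)/3 = 0.119 per year
- hazard ratio: ln(0.70)/ln(0.55) = 0.597

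Planned enrolment is given by "Eligible patients will be randomized in two arms in a ratio of 2:1 to reach an approximate total of 546 patients", split as "364 and 182 patients in the tegafur-uracil and observation groups, respectively". Expected events by 3 years are 182 × 0.45 + 364 × 0.30 = 191, which gives about 92% log-rank power at two-sided 0.05. The total of 546 is larger than these inputs need at 80% power (121 + 242 = 363 by the two-sided comparison of proportions). That is a separate matter and does not affect this point.

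**3. Illustration A: 55% and 70% read as recurrence-only**

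Assumption, not from the documents: recurrence-free death hazard d of 0.01 to 0.02 per year, equal in both arms. Then

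- DFS = exp(−3(h + d))
- HR = (0.119 + d)/(0.199 + d)
- recurrence-free deaths per arm = n × d/(h + d) × (1 − DFS)

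| | d = 0.01 | d = 0.02 |
|---|---|---|
| 3-year DFS, control | 53.4% | 51.8% |
| 3-year DFS, study | 67.9% | 65.9% |
| Recurrence-free deaths within 3 years | 13.1 | 25.9 |
| Share of all DFS events | 6.5% | 12.2% |
| HR with deaths counted | 0.616 | 0.633 |

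The recurrence-only figures are therefore higher by 1.6 to 3.2 points (control) and 2.1 to 4.1 points (study), and their HR is 0.597.

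With unequal risk, for example an assumed 3-year risk of 2% (observation) and 6% (study), DFS is 0.55 × 0.98 = 53.9% and 0.70 × 0.94 = 65.8%. The HR is 0.677 and power about 76%.

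**4. Illustration B: 55% and 70% read as DFS with deaths already included**

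The DFS hazard ratio is now 0.597, and removing deaths changes the recurrence-only ratio:

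| Assumed 3-year risk of recurrence-free death (observation / study) | Deaths not counted | Recurrence-only HR |
|---|---|---|
| 2% / 2% | about 9 (2.8 + 6.2) | 0.583 |
| 5% / 5% | about 23 (7.0 + 15.7) | 0.559 |
| 2% / 6% | about 22 (2.8 + 18.9) | 0.510 |

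**5. Direction**

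Write d_S and d_C for the recurrence-free death hazards in the study and control arms. Starting from recurrence hazards in the ratio 0.597, (0.119 + d_S)/(0.199 + d_C) exceeds 0.597 exactly when d_S/d_C exceeds 0.597. Below that, leaving deaths out makes the HR look less favourable.

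**6. The per-protocol rule**

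A patient who dies without recurrence in the first 12 months has not completed 12 months and is not covered by the exception for early recurrence. That patient leaves the main analysis whichever DFS definition is used. Correcting the definition alone would bring in only later deaths.

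**The case against.** The strongest reply is that the statistical section is the only place that formally defines 3-year DFS, that it counts deaths, and that the other section is merely loosely worded. The log-rank sentence comes before the DFS rule and covers OS as well, so it is not expressly tied to recurrence-only events. This reading is plausible. It does not remove the conflict, because the efficacy-endpoint section names death for OS and leaves it out for DFS, and nothing says which section governs.

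Three stronger readings are tempting, and the documents do not support them:

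- *Recurrence-free deaths are censored in the primary test.* No section states a censoring rule. Censoring is what would follow if the recurrence-only rule were used.
- *The recurrence-only rule hides fatal toxicity.* Deaths still count in OS, which this article calls primary in two sections and secondary in another, and they are reported as serious adverse events. For deaths in the treatment year, the per-protocol rule is what removes them from the main analysis.
- *The hazard ratio is flattered.* This holds only under the condition in step 5, and the documents give no rates by which to judge it.

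It is also fair to say that the effect is modest when mortality is equal. With the 202 to 212 events implied by illustration A, power is about 90% to 88%, still above the planned 80%. Finally, the Patient number section calls 55% and 70% DFS rates, so illustration A is only one of two readings.

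**Conclusion.** The concern holds as a contradiction in the definition of the primary endpoint. It is not something a condensed article may leave open, because the article states the event twice and differently. If the recurrence-only rule is used for the log-rank test, the test and the Kaplan-Meier estimate address different endpoints.

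Size and direction cannot be derived from the documents. Under constant hazards, equal recurrence-free mortality of 1-2% per year and 55%/70% read as recurrence-only, the gap is about 2-4 points in 3-year DFS and 0.616-0.633 against 0.597 in the hazard ratio. It grows if such deaths are more frequent in the study arm and can reverse if they are sufficiently rarer there. The contradiction itself depends on none of these assumptions.

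**What to change.** - In Efficacy measurements and endpoints, define DFS as the time from randomization to the first of recurrence or death from any cause. This matches the statistical section.
- State that this one event definition applies to both the log-rank test and the Kaplan-Meier estimate. Time to recurrence can be kept as a supportive analysis.
- In Patient number, state that the 55% and 70% refer to the same definition, or restate them if the retrospective data counted recurrence only.
- Extend the per-protocol exception from early recurrence or relapse to early death. Otherwise deaths in the first 12 months stay outside the main analysis even after the definition is corrected.

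The exact censoring date for patients alive without recurrence can be left to the statistical analysis plan.

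The cost is a few sentences. Dates of death are already needed for OS, so no new data are collected. If the planning rates prove to be recurrence-only, the expected DFS rates become slightly less favourable. The change should be made before outcome data are examined.
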